### Recruitment

Study participants will be recruited at social workers station in Shanghai. Drug abusers who are newly ordered to undergo community-based rehabilitation will be invited. Social workers who are trained will be responsible to provide consent and complete the screening tool. Recruitment has commenced and will continue until the end of 2018 or until our sample target is reached.

### Assignment of interventions

#### Allocation

Those that consent will be randomized using simple randomization tables generated by SPSS Statistics (version 22) (24); 35 subjects will be assigned to the usual group (routine community-based rehabilitation) and 35 to the integrated rehabilitation group (routine community-based rehabilitation + CAREs intervention).

#### Blinding

To minimize the risk of biased results as much as possible, the persons who conduct the urine tests and complete the evaluation of the ASI will be different from those who provide the intervention. But subjects may talk about the CAREs intervention during the assessment so it is not possible to completely “blind” the evaluators to the integrated rehabilitation group of the subjects.

### Data collection

The majority of study-specific data outlined in the protocol will be entered onto the paper Case Report Form (CRF) by site coordinators in accordance with the Clinical Completion Guidelines. Urine test data will be collected by each participant's corresponding social worker. These paper gees will be collected at each monitoring visit and double data will be entered by specialists. The CAREs usage data among integrated rehabilitation group will be collected automatically from the system, whereas those electronically data will be maintained on a secure server at SMHC and will be downloaded periodically for storage in a password-protected data file accessible by two study personnel.

### Data management

Intention-to-treat principle will be used in the statistical analysis. All statistical analyses will be conducted using SPSS Statistics (version 22) (24). Chi-square tests and ANOVAs will be used to compare characteristics of the members of the two groups. Primary outcome and secondary outcomes (results of urine illicit drug tests between the groups, the days that participants interact with their corresponding social workers) will be compared between groups using analysis of ANOVAs. Considering behavioral clinical trials often find data missing at the end of trials due to incomplete evaluations, Generalized Estimating Equations (GEE) will be used to compare the seven dimensions scores of the ASI between group across the study period. Any unfavorable changes to participants during the study period will be recorded. Since this study does not impact participants' routine care and is examining the effect of an integrated community-based rehabilitation for drug abusers in communities, no serious adverse events are anticipated and no interim analyses are planned.

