### Interventions

Participants who are newly enrolled in the standardized community-based rehabilitation will be designated to join the social worker organizations where the residence of the drug users are registered and have to sign a contract with their corresponding social workers. Participants need to visit their corresponding social workers and receive illicit drug test every 2 months. Social workers will help their corresponding clients to apply for social benefits accordingly and provide counseling irregularly if necessary.

The integrated rehabilitation group will receive the standardized community-based rehabilitation described above and simultaneously receive a 6 months integrated rehabilitation based on CAREs. CAREs was developed by the department of addiction research in Shanghai Mental Health Center (SMHC), with functions including education, support, psychological intervention and other functions.

The main structure of the system consists of three parts: (a) an APP for users; (b) a web page for service providers such as social workers; (c) server to store data and information (see Figure 1).

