### Outcomes

The primary outcome is the performance on urine drug screen (UDS) which will be carried out regularly during the study period twice per week. The results of urine tests will be examined in the difference of proportion of drug-positive samples between two groups. Urine test kit will be used to test drug use including heroin, amphetamine-type stimulants, marijuana, cocaine, and ketamine. A subject who does not submit urine samples during the intervention period or who refuses to submit a sample even if he/she is present at the site will be considered as having a positive UDS.

Secondary outcomes include: (a) longest duration of sustained abstinence, defined as the longest continuous record weeks of negative urine drug screen samples; (b) interaction with social workers in the addiction recovery services: the days that participants interact with their corresponding social workers will be collected during the study period. Any phone call, SMS, face-to-face meeting, or communication via CAREs will be considered as one interaction; (c) the decrease rate of addiction-related issues severity index: the Chinese translation of the Addiction Severity Index (ASI) that has good reliability and validity in China will be used to assess the severity of addiction at enrollment and 6 months after enrollment. The reliability and validity of the Chinese version of the instrument have been assessed (21, 22). The internal consistency of the seven dimensions was judged to be acceptable (alpha = 0.44~0.79), the test-retest reliability was good (ICC = 0.68~0.84), and the inter-rater reliability was good (ICC = 0.87~0.98). The descent rate will be counted via dividing the minus value between baseline score and 6 months score by baseline score (assessments completed at assessment phases shown in Table 3).

**Table 3 T3:** Assessments completed at assessment phases.

**Assessments**		**Assessment Phase**		
		**T1**	**T2**	**T3**

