### Participant timeline

Individuals who express interest will be invited to participate in informed consent procedures. Those who voluntarily consent to participate will then enter a 3 days screening to determine whether they meet inclusion/exclusion eligibility criteria. Baseline measurements of drug use and UDS will also be collected at this time. Participants who continue to meet eligibility criteria will participate in a 7 days induction period. During the induction period, participants and their corresponding social workers will be trained by technicians to get familiar with CAREs. Participants will be randomly assigned, in a 1:1 ratio, to receive either the intervention program or control program for a period of 6 months. Subsequent assessment points coincide for both groups at 6 months after randomization (see Figure 4).

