### Sample size

This is a pilot study design. Based on official records of the community-based rehabilitation program in Shanghai (23), the investigators estimated that the proportion of drug abusers in this program is around 40% and the proportion of loss-to-follow-up is 20%. Related literature pointed out that the use of mobile APP can result in a 60% reduction in substance use. Assuming α = 0.05, β = 0.10, a 70 participants sample size was calculated by sample size estimation for a comparison of two proportions. The sample size required for comparing the difference of performance on illicit drug urine test in two group (controlled group vs. integrated rehabilitation group) is 35 cases per group.

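### The primary urine-test outcome has no fixed unit of analysis: it is defined on samples, sized on persons, and assigned to an ANOVA that names neither

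*Protocol article*

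**What the plan says.** Three sections of the protocol article bear on the primary outcome.

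- **Outcomes.** The comparison is stated on samples: "The results of urine tests will be examined in the difference of proportion of drug-positive samples between two groups". Testing is "carried out regularly during the study period twice per week". A sample that is not submitted, or is refused, "will be considered as having a positive UDS".
- **Sample size.** The calculation is on persons: "a 70 participants sample size was calculated by sample size estimation for a comparison of two proportions", giving 35 per group. It gives no number of tests per person, no standard deviation and no within-person correlation.
- **Data management.** The urine results and the days of interaction with social workers "will be compared between groups using analysis of ANOVAs". No per-participant summary and no repeated-measures term is named for the urine results. GEE is named for the seven ASI scores only.

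Two further statements fix the number of tests. Participant timeline has participants assigned "to receive either the intervention program or control program for a period of 6 months". Interventions, describing standard rehabilitation, says "Participants need to visit their corresponding social workers and receive illicit drug test every 2 months", which is a different testing frequency from the one in Outcomes.

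**The concern.** The result of the primary comparison depends on its unit. Repeated urine tests from one person are alike: someone who is using tends to test positive repeatedly, and someone who is abstinent tends to test negative repeatedly. If the samples in each arm are pooled and compared as independent observations, the standard error is too small, the confidence interval too narrow and the p-value too low. If each participant contributes one percent positive, that problem goes away.

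The text does not say which of these is meant, and the sample-size section uses a third set-up, one yes/no result per person. Two analysts following the article could report very different p-values for the only primary outcome. The plan does name a method for correlated data, but gives it to the ASI, measured twice, and not to the outcome measured about 52 times.

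**Working it through.** **Inputs from the article.** Two tests per week (Outcomes); 6 months, taken as 26 weeks (Participant timeline); 35 per arm, a proportion of 40%, a 60% reduction, α = 0.05, β = 0.10 and 20% loss to follow-up (Sample size). The reduction is read as relative: 0.40 × (1 − 0.60) = 0.16.

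**Assumption.** The article gives no within-person correlation. ICC values from 0.1 to 0.9 are shown, the same in both arms.

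**1. The plan's own figure.** For 0.40 versus 0.16, two-sided α = 0.05 and 90% power, the mean proportion is 0.28, and the pooled formula for two independent proportions gives

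n = [1.96·√(2 × 0.28 × 0.72) + 1.2816·√(0.40 × 0.60 + 0.16 × 0.84)]² / 0.24² = 71.5, so 72 per arm.

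The unpooled formula gives 69. Neither is 35, and neither yet includes loss to follow-up. With 35 per arm this person-level test has about 61% power. That the stated figure does not reproduce is a separate defect. What matters here is that the calculation has one result per person.

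**2. Number of tests.** 26 × 2 = 52 per participant; 35 × 52 = 1,820 per arm.

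**3. Samples compared as independent.** Design effect DE = 1 + (52 − 1) × ICC. Effective samples per arm = 1,820 / DE. Actual error of a nominal 5% test = 2 × [1 − Φ(1.96/√DE)]. An ANOVA of 0/1 results with no participant term is, at this sample size, essentially this test.

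| Assumed ICC | DE | Effective samples per arm | Type I error |
|---|---|---|---|
| 0.1 | 6.1 | 298 | 43% |
| 0.3 | 16.3 | 112 | 63% |
| 0.5 | 26.5 | 69 | 70% |

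Beta-binomial simulation with 35 per arm and 52 tests each agrees: about 43%, 62–63% and 70%.

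**4. The same with the two-monthly schedule.** About 3 tests in 6 months gives DE = 1 + 2 × ICC, which is 1.2 at ICC 0.1 and 1.6 at ICC 0.3. The type I error is then about 7% and 12%.

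**5. One percent positive per participant, compared by ANOVA.** In simulation with 52 tests, type I error stays at about 5% (4.4% to 5.2%) for ICC 0.1 to 0.7. The variance of one participant's proportion is p(1 − p) × [ICC + (1 − ICC)/52]. For 0.40 versus 0.16:

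| Assumed ICC | Simulated power, 35 per arm | Evaluable per arm for 90% power (normal approximation) |
|---|---|---|
| 0.3 | 98% | 22 |
| 0.5 | 89% | 35 |
| 0.7 | 76–77% | 49 |
| 0.9 | 67% | 62 |

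At ICC 0.1 the requirement is about 9 per arm. A formula with one binary result per person contains neither the ICC nor the number of tests, so it cannot produce these figures.

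**The case against.** The strongest reply is that the planned test may be sound. Data management never says that the ANOVA is run on binary results or on samples. The same sentence applies ANOVA to days of interaction, which is one value per participant, so one percent positive per participant is a natural parallel. Chi-square, the obvious test for pooled positive and negative samples, is named only for comparing group characteristics. On that reading the error rate is about 5%, and ANOVA need not be replaced.

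This stands, and it limits the point. A reader might infer that the trial's planned test has a 43% to 70% false-positive rate. The article does not support that: the figure applies only if the comparison is made on samples, as the Outcomes section words it. Nor does it support saying that the analysis is deliberately unadjusted. No covariate is named, but a condensed article may leave covariates to the full protocol or SAP, and an unadjusted comparison in a randomised trial is unbiased in any case. Using the baseline UDS is a gain in precision, not a repair.

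The article also gives a reason for using GEE on the ASI, namely evaluations missing at the end of the trial. Missing urine samples are instead counted as positive. That explains the split of methods but does not deal with correlation among urine tests. Counting missing samples as positive would tend to add runs of identical results within a person.

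The power loss appears only at the higher assumed ICCs. At 0.3 power is above 90%, and at 0.5 it is close to it. That 35 per arm matches the requirement at ICC 0.5 is no evidence that the plan assumed this, since the article states another method.

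What the reply does not remove is the conflict in what the article states: an outcome on samples, a calculation on persons, and a test with neither unit attached.

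**Conclusion.** The point holds as a failure to fix the unit of analysis for the primary outcome, with a sample-size calculation that fits neither repeated-test analysis.

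- **Compared on samples, as Outcomes words it:** type I error is about 43% to 70% at assumed ICC 0.1 to 0.5 with 52 tests per person, or about 7% to 12% at ICC 0.1 to 0.3 with about 3 tests.
- **Compared on each participant's percent positive:** type I error is about 5%, and simulated power at 35 per arm with 52 tests is about 98%, 89%, 76–77% and 67% at ICC 0.3, 0.5, 0.7 and 0.9.

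These sizes rest on the assumed ICCs, on reading the 60% reduction as relative, and on all scheduled tests being counted. The power figures use all 35 participants per arm, with no allowance for the 20% loss. The number of tests depends on which schedule applies; Outcomes and Interventions differ and must be reconciled.

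**What to change.** 1. State that the participant is the unit of analysis for the primary outcome.
2. Name one analysis in advance. Either compare each participant's percent positive by ANOVA, or by ANCOVA with baseline UDS as covariate; or model all scheduled UDS results by a logistic GEE clustered by participant, with arm and baseline UDS and a robust standard error corrected for the small number of participants. Under either, report the difference in percent positive with a 95% confidence interval.
3. Restate the power in the Sample size section on that scale, with the number of tests per person and a range of ICCs. This does not require enrolling more participants.
4. Reconcile the testing frequency in Outcomes with that in Interventions, since the number of tests enters both the analysis and the power.

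The cost is a change of wording and minor analysis work. Baseline UDS is already collected and GEE is already in the plan. The downside is that the restated power may be less favourable than the 90% now claimed.

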**SECONDARY OUTCOMES**				
	Longest duration of sustained abstinence			X
	Interaction with social workers			X
	The decrease rate of addiction-related issues severity index			X

*T1: Baseline assessment*.

*T2: Duration of 6-month intervention*.

*T3: Completion of 6-month intervention*.

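### GEE is offered as the answer to missing end-of-trial ASI data, but with one post-baseline ASI it cannot recover loss caused by relapse after baseline

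*Protocol article*

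**What the plan says.** The Data management section gives both the method and its reason: "Considering behavioral clinical trials often find data missing at the end of trials due to incomplete evaluations, Generalized Estimating Equations (GEE) will be used". The comparison is of the seven dimension scores, over what the section calls the study period. The same section adopts intention to treat.

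The ASI schedule is in Outcomes, secondary outcome (c). The instrument "will be used to assess the severity of addiction at enrollment and 6 months after enrollment". The outcome itself is a relative change: "The descent rate will be counted via dividing the minus value between baseline score and 6 months score by baseline score". Table 3 lists "The decrease rate of addiction-related issues severity index" with a mark at T3 (end of intervention) only; during the intervention (T2) only the urine drug screen is marked. Participant timeline agrees: "Subsequent assessment points coincide for both groups at 6 months after randomization".

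Sample size assumes that "the proportion of loss-to-follow-up is 20" per cent. Discontinuation allows the investigator to withdraw a participant for rehabilitation failure, meaning incarceration or compulsory readmission, as well as for protocol deviation or at the participant's request. Withdrawal ends the study for that person. The one explicit missing-data rule, which counts an absent sample as positive, covers urine tests and not the ASI.

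**The concern.** A repeated-measures model helps with dropout when a lost participant leaves behind scores that predict the missing one. Here no post-baseline ASI precedes the final one, so the only ASI information a lost participant leaves is the enrolment score. If people leave because of what happened after enrolment, that score cannot stand in for the missing one.

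The article presents the ASI comparison as protected against end-of-trial missingness. If relapsers are the ones lost, the month-6 scores that remain are too favourable, and more so in the arm with more relapse. The estimated ASI difference would then be distorted while the text tells the reader that the problem has been handled.

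**Working it through.** The article states no figure that depends on this point, so there is none to reproduce. The check has three parts.

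**1. How many month-6 scores are missing.** Inputs: 35 per group and 20% loss (Sample size). Expected missing = 70 × 0.20 = 14, or 35 × 0.20 = 7 per arm if loss is equal. That leaves 56 with a month-6 ASI, 28 per arm.

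**2. What GEE does with two time points.** Simulation: 35 per arm, baseline and month 6, group-by-time model, 400 replicates, true effect zero, about 20% lost per arm. Assumptions not taken from the article: within-person correlation 0.5 and the dropout mechanisms. In the second and third rows, controls above the mean are lost at 40%, controls below it are never lost, and CAREs participants are lost at random. Bias is CAREs minus control at month 6, in SD units; the Monte Carlo standard error is about 0.013.

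| Dropout mechanism | Independence | Exchangeable |
|---|---|---|
| Random | 0.01 | 0.01 |
| Controls, by baseline score | 0.11 | −0.02 |
| Controls, by unseen month-6 score | 0.22 | 0.17 |

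Under independence the GEE month-6 difference equals the plain completer difference to machine precision. Under an exchangeable structure the lost participants' baseline records carry weight. They remove the bias from baseline-driven loss, within simulation error, but most of the bias from loss tied to the month-6 outcome remains.

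**3. Possible size.** Take drug use as 40% in controls, and read the 60% reduction in Sample size as 0.40 × (1 − 0.60) = 16% with CAREs. Assume the ASI difference between arms arises only through relapse, so that it is proportional to the difference in relapse shares. The true difference is 0.40 − 0.16 = 0.24. The loss rates below are assumed, and the shares are among those still assessed.

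*Scenario A: 35% of relapsers and 10% of others lost, in both arms.*
- Control: 0.40 × 0.65 / (0.40 × 0.65 + 0.60 × 0.90) = 0.26 / 0.80 = 0.325 (20% lost)
- CAREs: 0.16 × 0.65 / (0.16 × 0.65 + 0.84 × 0.90) = 0.104 / 0.860 = 0.121 (14% lost)
- Difference 0.204; 0.204 / 0.24 = 85%

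*Scenario B: 50% of relapsers and no others lost, in both arms.*
- Control: 0.20 / (0.20 + 0.60) = 0.250 (20% lost)
- CAREs: 0.08 / (0.08 + 0.84) = 0.087 (8% lost)
- Difference 0.163; 0.163 / 0.24 = 68%

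*Unequal loss by arm, using Scenario B's rate in one arm only.*
- Only control relapsers lost: 0.250 − 0.160 = 0.090, or 38% of the true difference
- Only CAREs relapsers lost: 0.400 − 0.087 = 0.313, or 130%

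If loss is unrelated to relapse, the shares stay at 0.40 and 0.16 and there is no bias.

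Part 3 computes completer shares and does not fit a GEE. It gives the GEE result exactly under independence. Under another structure it is close only so far as baseline ASI does not predict who relapses.

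**The case against.** The strongest reply is that GEE keeps the lost participants' baseline records, so its protection is partial rather than absent. That stands. A reader might infer that GEE gives no protection here, or is valid only if scores are missing completely at random. The documents do not support that: the article names no working correlation, weighting or covariates, and the exchangeable results show real correction of baseline-driven loss.

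Those details may also sit in an analysis plan that is not shown. That is fair, and their absence is not the point. The point is the reason the article gives for the method, set against its own assessment schedule.

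A reader might further infer that loss is shown to follow relapse. It is not. The 40–60% poor-outcome figure in the Introduction describes the background population, not reasons for a missing trial ASI. Discontinuation permits withdrawal for incarceration or compulsory readmission but does not require it, lists other reasons too, and does not list relapse alone. Outcome-related loss is plausible; its size and any difference between arms are unknown.

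Finally, the loss rates in Scenarios A and B are hypothetical, and the ASI covers seven dimensions, not relapse alone. With equal relapse-specific loss in both arms the error is attenuation, which is conservative in a superiority trial. The scenarios should not be read as predicting a false benefit.

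**Conclusion.** The point holds in a limited form. With a single post-baseline ASI, GEE can use baseline scores to correct loss that baseline explains, but it cannot recover loss caused by events after baseline. The decrease rate cannot be computed at all without the month-6 score. The article's reason for choosing GEE therefore promises more than its schedule can deliver.

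About 14 of 70 participants are affected at the planned loss. A shrinkage to 68–85% of the relapse-driven difference rests on the assumed loss rates, on reading the sample-size inputs as 40% against 16%, and on an ASI effect that works only through relapse. The bias is nil if loss is unrelated to relapse and can go in either direction if loss differs by arm.

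The scope is one secondary outcome in a study that calls itself a pilot. A reader might extend the point to the primary urine outcome, but that has its own rule for missing samples and is not touched here.

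**What to change.** For the ASI outcome:

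- Delete the wording that presents GEE as the means of dealing with end-of-trial missing data.
- Compare month-6 dimension scores between arms, adjusted for baseline ASI.
- Multiply impute missing month-6 scores from arm, baseline ASI, baseline urine drug screen and a low-dimensional summary of urine results before loss, such as the proportion positive among submitted samples. With about 28 completers per arm, some 50 separate urine results cannot be used as predictors. Samples counted as positive only because they were absent should stay out of the summary.
- Add a delta-shift sensitivity analysis that makes lost participants' imputed scores progressively worse, since imputation cannot reach loss that the observed data do not explain.
- Reconcile the urine-test frequency, because the imputation depends on it: Outcomes has testing twice per week, Interventions every 2 months.

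In a check of Scenario B with assumed effect sizes, completer and baseline-adjusted estimates fell to about 68–69% of the true difference, while imputation using the urine results recovered about 90%. The gain depends on how closely the observed urine results track relapse.

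The cost is revised analysis wording, a little programming and slightly wider intervals. No new data are needed if urine testing runs at the frequency given in Outcomes.

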## Abstract

**Introduction:** Relapse is very common in drug abusers and contributes to a series of negative consequences. Effective addiction treatment exists but there are some problems in the implementation process. Mobile health (mHealth) offers a potential solution to improving recovery outcome for drug abusers in the community. The research team developed a community-based addiction rehabilitation electronic system (CAREs). The primary aim of this study is to explore whether the integrated rehabilitation based on program CAREs promotes drug abusers to keep abstinence. The secondary aim is to evaluate the impact of CAREs on interaction between drug users and service providers, and on addiction-related physical and social functions.

**Method and analysis:** A randomized controlled trial (RCT) will be conducted. The study is a superiority trial with parallel group design. Seventy drug abusers who are newly ordered to undergo community rehabilitation will be recruited from the community in Shanghai. Participants will be 1:1 randomly assigned to receive integrated community rehabilitation by using CAREs or only receiving routine community rehabilitation for 6 months. Corresponding social workers will provide service and monitor their drug use behavior in accordance with the routine work-flow. Outcomes will be assessed at baseline and in the 6th month. The primary outcome is the performance on illicit drug urine test which will be carried out regularly twice per week during the study period. Secondary study outcomes include longest duration of sustained abstinence, days that participants interact with social workers, and the decrease rate of addiction-related issues severity index. Chi-square tests and ANOVAs will be used to compare characteristics of the members of the two groups. GEE will be used to compare the seven dimensions scores of the ASI between groups.

**Discussion:** The study provides evidence for the feasibility and effectiveness of the “CAREs” system through comparing the results of the intervention group with the control group. This paper describes the design and methodology of the study.

**Ethics and dissemination:** The Ethical Board of SMHC approved the study protocol. All participants will present for the informed consent process. After study completion, the results will be published.

**Trial Registration:** ClinicalTrials.gov NCT03451344, https://clinicaltrials.gov/ct2/show/NCT03451344

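### The ASI outcome is a fall from baseline, but the stated GEE compares scores between groups over both visits; month 6 adjusted for baseline would be more efficient at no cost

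*Protocol article*

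**What the plan says.** Secondary outcome (c) in the Outcomes section is "the decrease rate of addiction-related issues severity index". The ASI "will be used to assess the severity of addiction at enrollment and 6 months after enrollment", so each participant has at most two scores per dimension, one of them taken before treatment starts. The outcome is then built as a change from baseline: "The descent rate will be counted via dividing the minus value between baseline score and 6 months score by baseline score".

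The analysis is given in Data management. The motive is missing data ("Considering behavioral clinical trials often find data missing at the end of trials due to incomplete evaluations"), and the method is a GEE that "will be used to compare the seven dimensions scores of the ASI between group across the study period". The abstract puts it more briefly: "GEE will be used to compare the seven dimensions scores of the ASI between groups". Neither sentence mentions change, a time term, an interaction or adjustment for the baseline score. The article states no other analysis of the ASI.

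**The concern.** The outcome asks which arm improved more. The analysis sentence asks whether the arms' scores differ over the period. With only two visits, a between-group comparison over the period gives about half its weight to a score that CAREs cannot have influenced. A true month-6 difference is then diluted, and any chance baseline difference goes straight into the estimate.

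This is the only stated analysis for the part of the secondary aim that concerns addiction-related physical and social functions. With seven dimensions and a small trial, a diluted contrast could leave a real benefit undetected. Leaving the contrast open also leaves room to choose it after the data have been seen.

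**Working it through.** **Plan's own figure.** There is none to reproduce. The sample-size section covers the urine-test comparison only; no ASI effect, SD or power is given.

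**Inputs from the protocol.** Allocation is 35 per arm ("35 subjects will be assigned to the usual group (routine community-based rehabilitation) and 35 to the integrated rehabilitation group"). Loss to follow-up is 20% (Sample size), which leaves 35 × 0.8 = 28 completers per arm. There are two ASI visits.

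**Assumptions.** SD is 1 at both visits; the effect d occurs at month 6 only, with d = 0.8 or 0.5 SD; the baseline to month-6 correlation ρ is 0.3, 0.5 or 0.7; tests are two-sided at 0.05; a normal approximation is used. The Outcomes section reports test-retest ICCs of 0.68 to 0.84. These make a moderate or higher ρ plausible but do not establish it over six months of treatment.

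**Estimate and SD for each contrast (n per arm, SE = SD × √(2/n)).**
- Group term over both visits: expected value d/2, SD √((1+ρ)/2)
- Group-by-time (change): expected value d, SD √(2(1−ρ))
- Month 6 adjusted for baseline: expected value d, SD √(1−ρ²)

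**Worked case: n = 35, d = 0.8, ρ = 0.5.** √(2/35) = 0.239.
- Group term: z = 0.4/(0.866 × 0.239) = 1.93, power 49%
- Group-by-time: z = 0.8/(1.000 × 0.239) = 3.35, power 92%
- Adjusted: z = 0.8/(0.866 × 0.239) = 3.86, power 97%

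**Range.** Each cell gives power for group term / group-by-time / adjusted.

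| n per arm, d | ρ = 0.3 | ρ = 0.5 | ρ = 0.7 |
|---|---|---|---|
| 35, 0.8 SD | 55 / 81 / 94% | 49 / 92 / 97% | 44 / 99 / >99% |
| 35, 0.5 SD | 25 / 42 / 59% | 23 / 55 / 68% | 21 / 77 / 83% |
| 28, 0.8 SD | 46 / 72 / 88% | 41 / 85 / 93% | 37 / 97 / 99% |

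**Check by fitting the models.** Simulated data (600 replicates per cell, 35 per arm, 0.8 SD, exchangeable GEE with robust SE) gave 55%, 48% and 44% for the group term; 82%, 94% and 99% for group-by-time; and 91%, 97% and 100% for the adjusted analysis. With 20% of month-6 scores missing at random and ρ = 0.5, the figures were 40%, 86% and 91%.

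**Type I error.** A separate simulation with d = 0 (20,000 runs, 28 per arm) gave 4.9% rejection for the group term at ρ = 0.5 and at ρ = 0.7.

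**Efficiency relative to the adjusted analysis (ratio of squared z).**
- Group term: (1−ρ)/2, which is 35%, 25% and 15% at ρ = 0.3, 0.5 and 0.7
- Group-by-time: (1+ρ)/2, which is 65%, 75% and 85%

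**Chance imbalance.** A baseline difference b moves the expected group-term estimate by b(1+ρ)/2. One standard error of b at 35 per arm is 0.239 SD. At ρ = 0.5 the shift is 0.239 × 0.75 = 0.18 SD, against an expected signal of 0.4 SD when d = 0.8.

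**The case against.** The strongest reply is that the group main effect is an inference. The sentence names no model terms, and comparing two groups over a period can equally describe comparing their trajectories, which is a group-by-time GEE. The change-from-baseline definition in Outcomes favours that reading, and model terms are commonly left to a fuller document. This stands: the text does not show that a pooled comparison will be fitted. It does not dispose of the point, because the wording allows the poor contrast, and even the favourable reading is less efficient than adjusting month 6 for a baseline score that is collected anyway.

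A reader might infer that the plan tests a different null from the one it states. The document does not support that. It states no ASI hypothesis; the only one, in the Introduction, concerns urine tests. Under randomisation the expected baseline difference is zero, so the group term is zero in expectation exactly when the month-6 difference is zero. What changes is the scale of the estimate and the power.

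A reader might also infer that most of the power is lost whatever the data look like. That depends on ρ and on the comparator. Against group-by-time nothing is lost at ρ = 0. Where group-by-time has 80% power, the group term has 54% at ρ = 0.3 and falls below half of that 80% only once ρ exceeds about 0.45. Against the adjusted analysis there is a loss at every non-negative ρ: where that analysis has 80%, the group term has 51%, 38%, 29% and 19% at ρ = 0, 0.3, 0.5 and 0.7.

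Finally, this is described as a pilot, and the ASI is one of three secondary outcomes with no power claim. That limits the importance but not the case for a free correction.

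**Conclusion.** The point holds as a mismatch between outcome and analysis wording, with a better method available at no cost. If the sentence is followed literally, a month-6 difference d is estimated as about d/2. At 35 per arm and 0.8 SD, the power shortfall against the adjusted analysis is then about 39 points at ρ = 0.3 (94 − 55) and 48 points at ρ = 0.5 (97 − 49). If group-by-time was meant, the shortfall is smaller: about 13 points (94 − 81) and 5 points (97 − 92). Type I error is not at issue under either reading.

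These sizes rest on assumed effects and correlations, equal SDs, complete data and a normal approximation. They apply to the dimension scores, not to the percentage fall. The change should be made, but it concerns a secondary outcome and does not affect the primary comparison.

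**What to change.** In Data management, replace the ASI sentence with a statement that, for each ASI dimension, the treatment effect is the between-group difference at month 6 adjusted for that dimension's baseline score. If the two-visit GEE is kept, state that the conclusion rests on the group-by-time term and not on the group main effect. Bring the abstract into line.

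The cost is one sentence of analysis wording. The data, visits, participants and software stay the same.
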